## Outcomes

All feasibility outcomes will be assessed overall and by centre. Recruitment will take place for a minimum of 12 weeks and a maximum of 20 weeks, across the four maternity sites.

### Stop-go criteria

The decision to continue to a full trial will be decided by pre-defined stop-go criteria based on the following outcomes:The proportion of women randomised into the trial of the 250 recruitment targetThe proportion of women who received their allocated intervention out of all those randomisedThe proportion of women remaining in the trial (i.e. not withdrawn) who successfully complete the planned follow-up process for both the 14- and 30-day telephone interviewWithdrawal from the study

### Other feasibility outcomes

The proportion of eligible women approached to take partThe proportion of women randomised who have an elective/emergency CSThe proportion of women who are randomised into the PREPS trial with verbal consent from the number of women whom have an emergency CSThe proportion of women randomised who can successfully identify what treatment they received (i.e. vaginal cleansing or no vaginal cleansing)The proportion of complete data for each of the clinical and woman reported outcomes of women randomisedTime taken to perform the telephone interviewsReasons for withdrawal

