**Methods:**

This is a parallel group feasibility randomised controlled trial comparing vaginal cleansing using chlorhexidine gluconate versus no cleansing (standard practice) at CS to reduce infection. Women will be recruited from four National Health Service maternity units. Two hundred fifty women (125 in each arm) undergoing elective or emergency CS, who are aged 16 years and above, and at least 34 weeks pregnant will be randomised. Allocation to treatment will be on a 1:1 ratio. The study includes a qualitative aspect to develop women centred outcomes of wellbeing after delivery.

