## Methods

### Aims

The overarching aim of this research is to reduce infectious morbidity from caesarean sections. Specific objectives for this feasibility study include:To determine appropriate recruitment and randomisation processesTo assess if women can remain blinded to the trial interventionTo determine the sample size required for a definitive trialTo inform if the intervention can be conducted in a multi-centre RCTTo develop women focused outcome measures and method of data collectionTo assess data collection of clinical outcomes up to 6 weeksTo assess withdrawals

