### Blinding

The trial cannot be blinded to the operator or the clinical care team in theatre providing care to the women due to the nature of the intervention. Randomisation will be performed by a wide range of staff from theatre runners to consultants. Randomisation may be performed by dedicated research midwives who will also collect outcome data from the notes, but there will be no recording of the allocation in the post-natal notes.

Attempts will be made to blind the women as the intervention will be applied at the time of the catheter insertion, and the woman should not be aware of the application due to anaesthesia.

All data collection from the maternal notes will be blinded since there will only be recording of whether the intervention was applied on the theatre operation note and anaesthetic/operation chart, which are not held in the maternal post-natal notes. As a part of the monitoring process, 10% of medical records will be independently monitored and data collection will be verified by the trial sponsor on-site.

The research midwife conducting the telephone follow-up interviews will be blinded to the treatment group so that there will be no bias in the collection of outcomes. The research midwife will not have an access to the medical records or any data collection forms at the time of telephone interviews.

At the end of the 14-day interview, the midwife will ask the woman whether she feels she received the intervention or not to assess whether blinding of the woman is an achievable aim.

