### Intervention

Chlorohexidine gluconate 0.05% or chlorohexidine acetate 0.05% will be used to perform vaginal cleansing. The active ingredient is chlorhexidine 0.05%. This is indicated within the British National Formulary for swabbing in obstetrics.

Fifty millilitres of antiseptic (chlorohexidine gluconate 0.05% or chlorohexidine acetate 0.05%) will be emptied into a sterile pot. A single swab/sponge mounted on a sponge holder soaked in the antiseptic will be used to clean the vagina prior to CS at the time of urinary catheter insertion, for guidance, we suggest the vaginal cleansing should take 30 s. Following the CS procedure, the vagina will be cleaned of excess blood as is standard practice with a dry swab. The application of the intervention is quick and familiar to the doctors performing the surgery due to their experience in gynaecological surgery where it is routine practice. All theatres’ standard operating procedures regarding swabs and instrument counts should be adhered to, to ensure patient safety. At all sites, staff will be asked to record if they have performed vaginal cleansing, and if performed, which antiseptic was used, on the CS operation note within the hospital notes.

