### Analysis of outcome measures

A separate statistical analysis plan for the PREPS feasibility study will provide a detailed description of the planned statistical analyses. A brief outline of the planned analyses is given below.

All *clinical* outcomes will be analysed according to the treatment arm to which they were randomised (i.e. vaginal cleansing or no cleansing) irrespective of compliance with the randomised treatment allocation, as per the intention to treat principle. Women who did not undergo a CS will be excluded from the analyses.

All *feasibility* outcomes will be analysed pooling the two randomised groups and presenting overall estimates of proportions with 95% confidence intervals, as well as estimates by centre.

All outcomes will primarily take the form of simple descriptive statistics (e.g. proportions and percentages, means and standard deviations) and where appropriate, point estimates of effect sizes (e.g. mean differences and relative risks) and associated 95% confidence intervals.

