#### Traffic light system

Green light: recruitment rate > 90%, adherence rate > 75%, follow-up rate > 90% and dropout rate < 15%. If all four criteria are met, we will proceed to a full trial with the protocol unchanged (unless there is a clear message from the focus groups that would improve the protocol).

Amber light: recruitment rate 80–90%, adherence rate 50–75%, follow-up rate 75–90% or dropout rate 15–30%. If one or more of our amber light criteria are met, we will plan to adapt the protocol in light of the feedback from the focus groups and our experience to improve whichever criteria are not at the ‘green-light’ level before proceeding to full trial. We will assess whether adaption of the protocol will require a further feasibility study or pilot study before progressing.

Red light: recruitment rate < 80%, adherence rate < 50%, follow-up rate < 75% or dropout rate > 30%.

If one or more of these criteria are met, we would consider the current protocol not feasible and not progress to a full RCT.

The Trial Oversight Committee will take into consideration statistical uncertainty around these rates using 95% confidence intervals.

Missing data: Every attempt will be made to collect full follow-up data on all study participants; it is thus anticipated that missing data will be minimal and the strategies needed to achieve this are part of this feasibility RCT. The main analysis will use available data only; however, the amount of missing data will be assessed, and if necessary, sensitivity analyses will be undertaken.

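### The blinding measure has no fixed chance value and is pooled over arms, so its result may not show whether women stayed blinded

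*Protocol article*

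**What the plan says.** One stated objective (Aims) is to "assess if women can remain blinded to the trial" intervention. A single measure serves it. Under Other feasibility outcomes this is the proportion of "women randomised who can successfully identify what treatment they received", where the two possibilities are cleansing and no cleansing.

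Three other statements govern how the number is formed:

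- **Collection (Blinding).** At the end of the 14-day telephone interview "the midwife will ask the woman whether she feels she received the intervention or not". No other time of asking is described, and no answer category for women without an opinion is mentioned.
- **Missing data (end of Traffic light system).** "The main analysis will use available data only", with sensitivity analyses if needed.
- **Pooling (Analysis of outcome measures).** All feasibility "outcomes will be analysed pooling the two randomised groups and presenting overall estimates of proportions with 95% confidence intervals", plus estimates by centre. No estimate by arm is foreseen for these outcomes.

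The protocol gives no reference value for the blinding measure, and blinding is not one of the four stop-go criteria.

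**The concern.** A woman who is not reached at day 14 cannot enter the numerator. If the denominator is everyone randomised, she is counted together with the women who were asked and got it wrong. The proportion then mixes two things, how many women were reached and how well they knew their treatment, and the value expected under perfect blinding depends on the first.

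The available-data rule points to a different denominator, the women with an answer. The two statements are not reconciled. The wording of the measure cannot simply be taken as loose, because the follow-up criterion in the same article names a narrower denominator, women not withdrawn, where one is wanted.

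Pooling adds a separate difficulty. Only women in the cleansing arm can notice an application, so unblinding in one arm is a natural pattern to look for, and a pooled proportion does not show it separately.

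At stake is the reading of a named objective that informs the design of the definitive trial. The same percentage could mean sound blinding with good follow-up or failed blinding with poor follow-up.

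**Working it through.** The protocol states no figure for this measure, so there is none to reproduce.

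**Inputs from the protocol.** Target 250 women, 125 per arm, allocated 1:1 (Abstract; Feasibility study design). Green light: follow-up above 90% of women not withdrawn, dropout below 15%. Amber light: follow-up 75–90%, dropout 15–30% (Traffic light system).

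**Assumptions.** The undecided share *d* and the share correct among women who guess, *c*, are not given in the protocol and are varied below. The share interviewed, *f*, is taken at the edges of the traffic-light limits:

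- green limit: *f* = 0.85 × 0.90 = 0.765, about 191 of 250
- amber limit: *f* = 0.70 × 0.75 = 0.525, about 131 of 250

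These are worst cases within each band. The follow-up criterion requires both the 14-day and the 30-day call, so day-14 completion alone may be higher.

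**Literal measure** = *f* × (1 − *d*) × *c*. Percentages from counts use whole women out of 250, with Wilson 95% CIs.

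1. *Missing interviews only (d = 0).*
   - Green limit, pure guessing: 0.765 × 0.5 = 38.25% (96/250 = 38.4%).
   - Green limit, 70% correct: 134/250 = 53.6% (47.4 to 59.7).
   - Green limit, 90% correct: 68.8% (62.8 to 74.2).
   - Amber limit, all correct: 131/250 = 52.4% (46.2 to 58.5).
2. *Undecided answers only (everyone interviewed, d = 30%).* This dilution also applies under the available-data reading, if undecided women stay in the denominator.
   - 70% correct among guessers: 122/250 = 48.8% (42.7 to 55.0).
   - 80% correct among guessers: 140/250 = 56.0% (49.8 to 62.0).
3. *Both (green limit, d = 15%, c = 80%).* The literal measure is 130/250 = 52.0% (45.8 to 58.1). Among women who guessed it is 130/162 = 80.2% (73.4 to 85.6).
4. *Good follow-up (f = 95%, d = 15%, c = 80%).* 64.8% (58.7 to 70.5). Failed blinding is still visible.

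**Pooling.** With 1:1 allocation, complete data and a forced guess, let *a* and *b* be the probabilities of guessing cleansing in the cleansing and control arms. Then P(correct) = 0.5 + 0.5 × (*a* − *b*). With *a* = 0.8 and *b* = 0.5 this is 0.65: diluted from 80% in the cleansing arm, but not chance. Multiplied by 0.765 interviewed, it becomes 49.7%.

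With undecided answers, take the cleansing arm as 70% right, 5% wrong, 25% undecided, and the control arm as 30/30/40:

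- pooled proportion right among women interviewed: (0.70 + 0.30)/2 = 50%
- Bang's index (right minus wrong): 0.70 − 0.05 = 0.65 in the cleansing arm, 0.30 − 0.30 = 0 in controls

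The average undecided share here is (25 + 40)/2 = 32.5%, so pure guessing would give 0.675 × 0.5 = 33.75%. The 50% resembles chance only to a reader who applies a coin-toss benchmark, and the single pooled proportion does not supply the right one.

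**The case against.** The strongest reply is that the available-data rule already takes women without an interview out of the denominator. Nothing in the protocol says that women not reached are to count as blinded, and completeness of woman-reported data is a separate outcome. This stands in part: if the rule applies here, the missing-interview effect disappears. But the rule and the definition then name different denominators, and neither undecided answers nor pooling is dealt with.

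Second, undecided answers are not in the protocol, which describes a received-or-not question. That is right, so every figure with *d* above zero is conditional on an assumption. The amber-limit figure of 52.4% needs no undecided answers.

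Third, the analysis section is an outline, and by-arm tables belong in the analysis plan. An omission could be left there. Here, however, pooling is an explicit rule for all feasibility outcomes, and the denominator is written into the definition.

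Two further inferences are tempting but not supported. A reader might infer that control women will be confused because after surgery "the vagina will be cleaned of excess blood as is standard practice with a dry swab". The article only paraphrases the interview question, and nothing shows that women are aware of the swab. A reader might also infer that the proposed primary outcome of the full trial rests on women's telephone reports. The article defines it by the CDC criteria, places diagnoses that cannot be verified against them in a separate outcome, and does not tie endometritis to the calls.

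**Conclusion.** The point holds in a limited form. The protocol leaves two denominators unreconciled for its only blinding measure and pools that measure over arms. Under the literal denominator the chance value moves with follow-up, so that at the edges of the protocol's own bands about 38% can mean pure guessing and about 52% can mean complete unblinding. Under the available-data reading, undecided answers still lower the figure by an amount that cannot be stated in advance.

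A reader might infer that the measure will make failed blinding look like chance, or that pooling by itself hides unblinding in one arm. Neither follows. With 95% interviewed and 15% undecided, 80% correct still shows as 64.8%. Pooling alone dilutes one-arm unblinding and can mask it only together with missing or undecided answers. The protocol also sets no 50% benchmark and attaches no progression decision to this number. The consequence is a named objective whose answer may be hard to interpret, not a wrong stop-go decision.

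**What to change.** - Reconcile Other feasibility outcomes with the available-data rule by making the women asked the question at day 14 the denominator, and state how many randomised women were not asked.
- Exempt this outcome from the pooling rule in Analysis of outcome measures.
- Record don't know as an answer, and tabulate right, wrong, don't know and not asked by arm.
- Report a blinding index per arm, such as Bang's, with 95% CI. Read the two together: an index of 0.6 in one arm and −0.6 in the other reflects a belief shared by both arms, not knowledge of allocation.

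**Cost.** One answer option on an existing call, one amended definition and one table. The price is precision. With 191 women interviewed, the approximate 95% half-width for a proportion near 50% is 1.96 × √(0.25/191) = 7.1 percentage points pooled, against 1.96 × √(0.25/95.5) = 10.0 points per arm.

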### Clinical outcomes

The following clinical outcomes will be collected to inform sample size calculations for the main RCT.

#### Development of CDC defined endometritis in the post-natal period (days 0–30)

The development of endometritis meeting the CDC definition, in the post-natal period (day 0 of delivery), is the proposed primary outcome for the full RCT. Endometritis will be defined as per the definitions set out by the US Centre’s for Disease Control and Prevention (Centre’s for Disease Control and Prevention 2017) [10].

#### Clinical diagnosis of endometritis in the post-natal period (days 0–30)

Diagnosis of endometritis by a clinician which does not meet the CDC definition or cannot be verified to meet the definition, e.g. a woman treated in the community for suspected endometritis where it is not feasible to establish that this meets the CDC definition or where the diagnosis does not meet the criteria.

#### Maternal sepsis (days 0–42)

Defined according to the NICE sepsis guideline (released July 2016) [10].

#### Length of hospital stay

The length of hospital stay from randomisation to discharge home or transfer to another hospital following CS or up to 6 weeks after randomisation if not discharged.

#### Readmission to hospital after CS for suspected or confirmed infection (days 0–42)

It is defined as readmission to hospital post-discharge home up until 6 weeks postnatally.

#### Antibiotic prescriptions

These are antibiotics prescribed as an inpatient and hospital prescribed outpatient (days 0–42) and antibiotic prescriptions for suspected/confirmed surgical site infection relating to the woman’s CS (uterine, pelvic, abdominal wound and perineal).

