### Eligibility criteria and co-enrolment

Women will be included in the trial if they are as follows:Greater than or equal to 34 weeks pregnantHaving a CSAble to give informed written consentAble to receive a telephone interview at 14 and 30 days post-natalAged 16 years or over

Women will be excluded from the trial if they:Have a known allergy to chlorhexidine gluconate or any of its ingredientsAre receiving prophylactic intravenous antibiotics for group B streptococcus (GBS) colonisationAre receiving intravenous antibiotics for suspected infection (standard CS intravenous prophylaxis is not an exclusion criteria)Are currently enrolled in an RCT for an intervention intended to reduce post-operative surgical site infection

All women already enrolled in an interventional study are permitted to be co-enrolled into PREPS, as long as the intervention is not intended to reduce infection. After consent and randomisation to PREPS, women will not be permitted to enter a further interventional study if the study is evaluating the prevention of infection. Co-enrolment in all observational studies is permitted.

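### The first part of the antibiotic outcome does not exclude routine caesarean prophylaxis, so a yes/no count would approach 100% in both arms; three neighbouring outcome definitions need smaller repairs

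*Protocol article*

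**What the plan says.** All places are in the Protocol article.

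- **Antibiotic prescriptions.** The first part is "These are antibiotics prescribed as an inpatient and hospital prescribed outpatient", days 0–42. The second part is "antibiotic prescriptions for suspected/confirmed surgical site infection relating to the woman’s CS".
- **Eligibility criteria and co-enrolment.** Women on intravenous antibiotics for suspected infection are excluded, but "standard CS intravenous prophylaxis is not an exclusion criteria".
- **Clinical diagnosis of endometritis.** The outcome is "Diagnosis of endometritis by a clinician which does not meet the CDC definition or cannot be verified to meet the definition". CDC-defined endometritis, the proposed primary outcome of the full trial, is a separate outcome over the same days 0–30.
- **Length of hospital stay.** It runs "from randomisation to discharge home or transfer to another hospital following CS", or to 6 weeks after randomisation if the woman has not been discharged.
- **Readmission.** The section heading limits the outcome to suspected or confirmed infection. The sentence beneath says "It is defined as readmission to hospital post-discharge home up until 6 weeks postnatally".
- **Use of these outcomes.** The Clinical outcomes section says they are collected to inform the sample size of the main trial. Analysis of outcome measures plans descriptive statistics by randomised arm and, where appropriate, relative risks with 95% confidence intervals.

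**The concern.** The authors set prophylaxis aside when they wrote the eligibility exclusions, but did not do so when they wrote the antibiotic outcome. Day 0 is the day of delivery, so a prophylactic dose at the operation falls inside the window. Lower antibiotic use is one of the priorities given in the Background. A measure that almost every woman meets cannot show it.

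Three other definitions could mislead in lesser ways. Clinical endometritis is what remains after CDC cases are taken out, so its between-arm ratio cannot be interpreted alone. The stay stops at transfer, and readmission starts only after discharge home, so inpatient care after a transfer is counted in neither. The readmission definition sentence leaves out the cause that its heading gives.

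What is at stake is the usefulness of these summaries for planning the full trial, and the risk that the wording is carried into it.

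**Working it through.** **1. The plan's own figure.** Inputs from the Sample size section: 8.3% versus 4.3%, 90% power, alpha 5% (taken as two-sided), with 1:1 allocation assumed for the full trial as in this one. With pooled variance under the null and no continuity correction:

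n per arm = [1.960·√(2·p̄(1−p̄)) + 1.282·√(p₁(1−p₁)+p₂(1−p₂))]² / (p₁−p₂)², where p̄ = 0.063

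= [1.960·√0.11806 + 1.282·√0.11726]² / 0.040², which rounds up to 774

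Total 2 × 774 = 1548, and 1548/0.90 = 1720. Both stated figures reproduce. They rest on endometritis rates alone, so none of the four definitions changes them.

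**2. First part of the antibiotic outcome.** The documents give neither a therapeutic prescribing rate nor the share of women who receive prophylaxis. As an illustration, assume therapeutic prescribing at the endometritis rates (8.3% and 4.3%), and let an independent share b of women in each arm have an antibiotic not given for infection. The proportion scored yes is q = 1 − (1−p)(1−b).

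| b | Control | Cleansing | Risk ratio |
|---|---|---|---|
| 0 | 8.3% | 4.3% | 0.52 |
| 5% | 12.9% | 9.1% | 0.71 |
| 20% | 26.6% | 23.4% | 0.88 |
| 50% | 54.2% | 52.2% | 0.96 |
| 95% | 95.4% | 95.2% | 0.998 |
| 100% | 100% | 100% | 1.00 |

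The absolute difference shrinks from 4.0 points to 4.0 × (1−b). Routine prophylaxis puts b near the bottom of the table. The second part of the outcome names its indication, so b does not enter it.

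**3. Clinical endometritis as a remainder.** The rates here are invented to show the mechanism. Suppose control has 6% CDC-defined plus 4% clinician-diagnosed only, and cleansing has 3% plus 5%. The remainder alone gives 5/4 = 1.25. Any endometritis gives (3+5)/(6+4) = 0.80. The two ratios point in opposite directions because a CDC case counts as a no in the remainder.

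**4. Stay and readmission side by side.** A woman transferred to another hospital ends her stay on that day. She has not gone home, so her time in the second hospital is not a readmission. Neither outcome counts it.

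**5. Readmission heading against sentence.** The heading carries the infection restriction and the sentence does not repeat it. The critical care definition does write the restriction into its own sentence.

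**The case against.** The case against is substantial, and several parts of it stand.

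- The second part of the antibiotic outcome already gives an infection-specific measure, so antibiotic use for infection is not lost altogether. This stands, and it confines the main point to the first part.
- The article does not say that the first part will be scored yes/no, and a full protocol, case report form or statistical analysis plan may exclude prophylaxis. This limits certainty. The article nevertheless states the definition, and that definition contains no exclusion.
- A reader might infer that readmission is all-cause. The documents do not support that: the heading is part of the definition and restricts it to infection. Only a wording alignment remains.
- A reader might infer that all four definitions fail to isolate infection. They do not. Clinical endometritis is an infection diagnosis and a deliberate complement to the CDC outcome. Length of stay is a resource measure that was never meant to isolate infection.
- The two endometritis categories are mutually exclusive and can be summed, so no information is lost. This is true, but no combined outcome is listed, while relative risks by arm are planned where appropriate.
- The article gives no transfer frequency and does not say that transferred women are the sickest. Bias by severity is therefore possible but not shown. Starting the stay at randomisation applies equally to both arms and is defensible.
- The study is not powered for efficacy, and its summaries are mainly descriptive. That limits the consequence but does not repair the wording.

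**Conclusion.** The point holds in a limited form. As written, the first part of the antibiotic outcome admits routine prophylaxis. Scored yes/no, it would approach 100% in both arms with a risk ratio near 1. This assumes that most women receive prophylaxis, which the article implies but does not quantify, and that no document outside the article excludes it. The figures 0.52 to 1.00 illustrate the dilution and are not estimates for this trial.

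Three smaller points stand beside it. The remainder definition of endometritis needs an inclusive companion (the 1.25 versus 0.80 contrast is hypothetical). Inpatient care after transfer falls between two outcomes. The readmission sentence should match its heading.

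It would be wrong to conclude that progression or the planned trial size is compromised. The stop-go criteria use recruitment, adherence, follow-up and drop-out only. The 1548 and 1720 figures come from published endometritis rates. The proposed primary outcome is also unchanged.

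**What to change.** 1. **Antibiotics.** In the first part, exclude standard CS prophylaxis and count therapeutic courses only. Leave the second part as it is. Cost: wording in the protocol, case report form and analysis plan.
2. **Endometritis.** Add any endometritis (CDC-defined or clinician-diagnosed), days 0–30, reported by arm, and show the split between CDC-defined and other cases descriptively. Cost: none in data, since both components are already collected.
3. **Length of stay.** Carry the stay through any transfer to final discharge home, capped at 6 weeks. Cost: obtaining a discharge date from the receiving hospital for transferred women.
4. **Readmission.** Repeat the heading's infection restriction in the definition sentence. Cost: a few words.

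Recruitment had already opened when the article was submitted, so record the changes as dated clarifications before any comparison by arm is seen.
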